#### 7.5.4 Assessments during the 9-month follow-up after the end of the intervention

Patients from both groups will undergo a follow-up assessment, realized similarly three times:

- within one week after completing the 12-week online cognitive stimulation program (T1)
- 3 months (T2) after the end of the program
- and 9 months (T3) after the end of the program

These follow-up assessments will be realized on site, and will be planned, if possible, in the same time of a standard care visit. In the case the patient will have to come on site for a protocol-specific follow-up assessment, a compensation of 30€ /visit will be proposed to the patient)

Evaluations will include, on site:

- The completion of self-administered questionnaires to assess:
  - **Cognitive complaints**, using the FACT-Cog self-report questionnaire
  - **Quality of life**, using the FACT-G and EQ-5D-5L self-report questionnaires
  - **Sleep quality**, using the ISI self-report questionnaire
  - **Fatigue level**, using the FACIT-F self-report questionnaire
  - **Anxiety/Depression level**, using the HADS self-report questionnaire
  - **Physical activity level**, using the IPAQ self-report questionnaire
  - **Return to work**: date of return to work, and conditions of return to work (full or part-time, teleworking, professional retraining...)
- **Delivery of patient diary at T0, T1 and T2**
- **Laboratory Assessments similarly as at baseline at the end of the programme, then 3 and 9 months after the end of the cognitive stimulation programme.:**
  - Hematology (CBC, platelets, hemoglobin)
  - C-reactive protein
  - Serum biochemistry (Sodium, potassium, chloride, calcium, creatinine, glucose, ferritin)
  - Thyroid-function testing: thyroid-stimulating hormone [TSH]

**At the end of the 12-week intervention only (T1)**, a new optional biological collection will be set up for future investigations from a blood sample (6 x 5 ml tubes).

Additionally, participants will complete:

- **The CNS Vital Signs neuropsychological testing battery** to evaluate objective cognitive functions. This will be a self-administered test on their personal computer at home, with instructions provided by a clinical research assistant via an information booklet prior to the test.
- **At the end of the 12-week intervention only (T1)**, patients will be asked to assess their satisfaction with regard to the intervention using a specific questionnaire for each modality of intervention.

## 7.6 CRITERIA FOR PREMATURE WITHDRAWAL.

The intervention will be discontinued in the following scenarios:

- Patient's decision (previously collected data can still be used unless the patient objects)
- Inter-current illness or other reasons that require stopping the participation to the study
- Patient becoming untraceable
- Investigator's decision

In the event that a patient chooses to withdraw from the intervention program early, they will still be monitored unless they withdraw from the study altogether.

## 8 COGNITIVE EXERCISES

Both groups of patients will use the online version of the **HAPPYNeuron PRESCO** platform for **cognitive exercises**. This program was developed by the French neurologist B. Croisile, in French, and is available in 11 languages allowing a comparison of results between international studies. It has been used in several clinical studies, including with breast cancer patients (Damholdt et al., 2016). It has also already been used by the sponsor team in a feasibility study with patients treated with radiotherapy for a breast cancer (Binarelli, Lange, et al., 2021), and a feasibility study with patients over 70 years old and in the cognitive workshops promoted at the centre for all patients reporting cognitive difficulties. In all cases, patients provided positive feedbacks concerning the use of the software. This program has been specifically developed to train, through its 41 ludic exercises and 9 levels of difficulty, a wide range of cognitive domains (12 in total) including the most impaired after cancer treatments: attention, memory, executive functions and processing speed (Joly et al., 2015; Lange, Licaj, et al., 2019). Due to its broad range of targeted cognitive domains and intuitive user interface, it is well-suited for this clinical study. A table detailing the cognitive exercises available to participating patients is provided below.

| Cognitive domains trained    | Exercises                                                                                                                 |                                                                                                                                                |
|-------------------------------------|----------------------------------------------------------------------------------------------------------------------------------|------------------------------------------------------------------------------------------------------------------------------------------------|
| Memory (verbal and visual)   | Words, Where are you?
Elephant Memory
Shapes and Colours
Heraldry
Displaced Characters
Displaced Images
N-Back | Around the World in 80 trips
I Remember You!
Restaurant
An American in Paris
Find Your Way!
Chunking
Objects, Where are You? |
| Executive functions          | Towers of Hanoi
Basketball in New-York                                                                                        | Hurry for Change!                                                                                                                              |
| Attention                    | Pay Attention!
Private Eye!                                                                                                   | Ancient Writing                                                                                                                                |
| Information processing speed | Under Pressure                                                                                                                   | Gulf Stream
Catch the Ladybug!                                                                                                              |
| Language                     | Split words
Embroidery
Secret files
Speak Your Mind!                                                                    | Decipher
Writing in the Stars
This Story is Full of Blanks!
Which One is Alike?                                                       |
| Logic                        | The Right Count                                                                                                                  | Ready, Steady, Count!                                                                                                                          |

|                               |                                       |                                         |
|-------------------------------|---------------------------------------|-----------------------------------------|
|                               | Countdown                             |                                         |
| visuospatial abilities | Sleight of Hands
Entangled Figures | Point of View
Turn Around and Around |

## 9 TOOLS FOR ASSESSMENTS

### 9.1 COGNITIVE COMPLAINTS: THE FACT-COG SELF-QUESTIONNAIRE

After inclusion, patients' **cognitive complaints** will be evaluated using the self-report questionnaire **FACT-Cog**. It is a standardized and validated measure developed through interviews with expert clinicians and cancer patient focus groups (Joly et al., 2012; Wagner et al., 2009) and is widely used in clinical practice for evaluating patients' cognitive complaints during and after chemotherapy. It consists of four subscales:

1. *Perceived Cognitive Impairment (PCI, score range 0-72)*
2. *Perceived cognitive abilities (PCA score range 0-28)*
3. *Impact on quality of life (QOL score range 0-16)*
4. *Comments from others (OTH score range 0-16)*

Each item requires the patient to indicate on a 5-point Likert scale how frequently a particular situation has occurred in the past seven days.

### 9.2 OBJECTIVE COGNITION FUNCTIONS: THE CNS VITAL SIGNS BATTERY

The **CNS Vital Signs (CNS VS)** battery will be used to measure subtle cognitive performances differences inter and intra-group before and after intervention. This allow for easy cognitive assessment, without needing the presence of a neuropsychologist, as the test will be self-administered on a personal computer at home, with instructions provided by a clinical research assistant via an information booklet prior to the test. In addition, patients will be sent an email containing a link to access the test, a password, and guidelines to finish the 30-minute evaluation. The battery includes tests commonly used in neuropsychology, such as symbol digit coding, the Stroop test and finger tapping. Its test-retest reliability, concurrent validity with traditional tests, and discriminant validity were evaluated and found to be similar to those of traditional neuropsychological tests. The battery consists of 7 main tests that take approximately 30 minutes to complete.

- ❖ **Verbal Memory (VBM):** VBM measures recognition memory for Words. Fifteen words are presented, one by one, on the screen every two seconds. For immediate recognition, the participant has to identify those words nested among fifteen new words. Then, after six more tests, there is a delayed recognition trial.
- ❖ **Visual Memory (VIM):** VIM measures recognition memory for Figures or Shapes. Fifteen geometric figures are presented, one by one, on the screen. For immediate recognition, the participant has to identify those figures nested among fifteen new figures. Then, after five more tests, there is a delayed recognition trial.
- ❖ **Finger Tapping (FTT):** FTT test requires subjects to press the Space Bar with their right index finger as many times as they can in 10 seconds. They do this once for practice, and then there are three test trials. The test is repeated with the left hand.
- ❖ **Symbol Digit Coding (SDC):** SDC test consists of serial presentations of screens, each of which contains a bank of eight symbols above and eight empty boxes below. The participant types in the number that corresponds to the symbol that is highlighted. The computer program does not allow a person to use a numerical pad preventing a distinct advantage for those who are skilled at using the numerical pad or for those that are right- versus left-handed.
- ❖ **Stroop Test (ST):** In the first part, the words RED, YELLOW, BLUE, and GREEN (printed in black) appear at random on the screen, and the participant presses the space bar as soon as the test subject sees the word. In the second part, the words RED, YELLOW, BLUE, and GREEN appear on the screen, printed in colour. The participant is asked to press the space bar when the colour of the word matches what the word says. In the third part, the words RED, YELLOW, BLUE, and GREEN appear on the screen, printed in colour. The participant is asked to press the space bar when the colour of the word does not match what the word says.
- ❖ **Shifting Attention (SAT):** SAT test is a measure of ability to shift from one instruction set to another quickly and accurately. Participants are instructed to match geometric objects either by shape or by colour. Three figures appear on the screen, one on top and two on the bottom. The top figure is either a square or a circle. The bottom figures are a square and a circle. The figures are either red or blue (mixed randomly).

The participant is asked to match one of the bottom figures to the top figure. The rules change at random (i.e. match the figures by shape, for another, by colour).

- ❖ **Continuous Performance (CPT):** CPT test is a measure of vigilance or sustained attention. The test subject is asked to respond to the target stimulus “B” but not to any other letter. The stimuli are presented at random.

### 9.3 QUALITY OF-LIFE: THE FACT-G AND THE EQ-5D-5L SELF-QUESTIONNAIRES

#### ❖ *FACT-G self-report questionnaire*

Quality of life will be evaluated by using the **FACT-G** self-report questionnaire (D. F. Cella et al., 1993), which is a 27-item compilation of general questions divided into four primary QOL domains: Physical Well-Being, Social/Family Well-Being, Emotional Well-Being, and Functional Well-Being. It is considered appropriate for use with patients with any form of cancer, and has also been used and validated in the general population (using a slightly modified version).

#### ❖ *EQ-5D-5L self-report questionnaire*

In addition, quality of life will be also assessed through the French version of the five-level version of **EQ-5D** self-questionnaire (EQ-5D-5L), notably for the purpose of health-economics analysis. The EQ-5D is a generic instrument for describing and valuing health. It is based on a descriptive system that defines health in terms of 5 dimensions: Mobility, Self-Care, Usual Activities, Pain/Discomfort, and Anxiety/Depression (Brooks, 1996).

### 9.4 QUALITY OF SLEEP: THE INSOMNIA SEVERITY INDEX (ISI) SELF-QUESTIONNAIRE

**Quality of sleep** will be evaluated through the **Insomnia Severity Index (ISI)**. This 7-item self-report questionnaire was designed to assess the severity, underlying factors and impact of insomnia and to monitor treatment response in adults (Morin et al., 2011). It allows to evaluate 6 domains of insomnia: Severity of sleep onset, sleep maintenance and early morning waking problems, sleep dissatisfaction, interference of sleep difficulties with daytime functioning, noticeability of sleep problems by others, distress caused by the sleep difficulties.

### 9.5 FATIGUE: THE FUNCTIONAL ASSESSMENT OF CHRONIC ILLNESS THERAPY FATIGUE (FACIT-F) SUBSCALE

**Fatigue** will be evaluated by the completion of the **FACIT-F subscale**. This 13-item self-report questionnaire assesses self-reported fatigue and its impact on daily activities and function. It was originally developed as an addition to the Functional Assessment of Cancer Therapy (FACT) measurement system (D. Cella et al., 2002).

### 9.6 ANXIETY/DEPRESSION SYMPTOMS: THE HOSPITAL ANXIETY AND DEPRESSION SCALE (HADS)

**Level of anxiety and depression** will be evaluated by the **HADS**. This 14-items self-report questionnaire was originally developed by Zigmond and Snaith (1983) (Zigmond & Snaith, 1983) and is commonly used in the clinical practice to screen level of anxiety and depression in patients with various medical conditions.

### 9.7 LEVEL OF PHYSICAL ACTIVITY: THE INTERNATIONAL PHYSICAL ACTIVITY QUESTIONNAIRE (IPAQ)

**Level of physical activity** will be screened using the **IPAQ** (Craig et al., 2003). This standardized open-source self-report questionnaire provides an estimation of physical activity (intense, moderate and walking activities) and sedentary behaviour (sitting time) for adults across a range of socio-economic settings. The IPAQ short-form assesses the last 7-days physical activity undertaken across a comprehensive set of domains including: a. leisure time physical activity b. domestic and gardening (yard) activities c. work-related physical activity d. transport-related physical activity. The specific types of assessed activities are walking, moderate-intensity activities and vigorous-intensity activities.

### 9.8 SOCIO-PROFESSIONAL CONDITIONS

Socio-professional conditions will be assessed with a home-made questionnaire assessing notably date of return to work, and conditions of return to work (full or part-time, teleworking, professional retraining...)

## 10 SAFETY conducted as care vigilance

In accordance with the new research regulation involving the human person, there will be no collection of serious adverse events organized by the sponsor as part of the study.

However, as for all research involving the human person, the sponsor will transmit to the investigators concerned any information likely to affect the safety of persons (Art R1123-52 CSP) and will inform without delay the competent authority and the protection committee of new safety facts and, where appropriate, measures taken (Article R1123-59 of the CSP).

Nevertheless, health professionals are reminded that care vigilance applies, as a result any incident or adverse reaction suspected to be due to a drug or other health product as defined in Article L5311- 1 must be reported by the health professional to the vigilance networks (internet Portal for reporting adverse health events) who, after analysis, report them to the ANSM.

## 11 MEDICO-ECONOMIC STUDY

We will conduct a within-trial cost utility analysis using standard methods, comparing neuropsychologist-supervised online cognitive stimulation to unsupervised open access online cognitive stimulation program from the societal perspective. Outcomes will be reported as quality-adjusted life years (QALYs) and cumulative costs, undiscounted due to the 1-year time horizon (3 months intervention + 9 months follow up).

Costs: We will estimate costs for all healthcare use in both arms, including:

- labor costs for the supervised cognitive stimulation;
- physician services;
- hospitalizations, emergency visits;
- outpatient diagnostic tests;
- drugs, including the use of psychotropic drugs;
- home care;
- health-related out-of-pocket costs
- productivity costs.

Valuation will be conducted using national costs for hospital admissions, the social health insurance for services and purchase prices for drugs. Productivity losses will be valued by the mean per capita GDP.

The table below summarizes resource data collection and valuation

| Costs                                                                                                                                                  | Source of resource use                                                   | Valuation                                                                                                                                                                                                                             | Point of View                                              | Notes                                                                                          |
|--------------------------------------------------------------------------------------------------------------------------------------------------------|--------------------------------------------------------------------------|---------------------------------------------------------------------------------------------------------------------------------------------------------------------------------------------------------------------------------------|------------------------------------------------------------|------------------------------------------------------------------------------------------------|
| Medical costs                                                                                                                                          |                                                                          |                                                                                                                                                                                                                                       |                                                            |                                                                                                |
| Hospitalisations & outpatients visits post discharge                                                                                                   | eCRF DRG* & length of stay adverse events information                    | DRG - French national cost study (ENC)                                                                                                                                                                                                | Production costs to the hospital                           |                                                                                                |
|                                                                                                                                                        |                                                                          | DRG using average reimbursement by the national health insurance*                                                                                                                                                                     | Payer - national health insurance                          |                                                                                                |
|                                                                                                                                                        |                                                                          | DRG using average amount not reimbursed by the national health insurance*                                                                                                                                                             | Payer - patient out of pocket and private health insurance |                                                                                                |
| Consultations and medication in ambulatory care - Out of hospital care post discharge: only in relation with the follow up of the cognitive complaints | eCRF prescription information not in study centre collected from patient | Operative public sector 1 tariffs for physicians using the Nomenclature Generale des actes professionnels and the Ameli/Assurance Maladie reimbursement tariffs for the type of physician as recorded in the eCRF and pharmacy prices | Payer - national health insurance                          | Reimbursement rates at time of data analysis                                                   |
|                                                                                                                                                        |                                                                          |                                                                                                                                                                                                                                       | Payer - patient out of pocket and private health insurance |                                                                                                |
| Emergency room visits to centre not leading to hospitalisations                                                                                        | eCRF adverse events information                                          | Cours des Comptes average cost estimate of a visit                                                                                                                                                                                    | Production costs to the hospital                           | Emergency visits that lead to hospitalisations are included in the DRG for the hospitalisation |
|                                                                                                                                                        |                                                                          | Flat fee                                                                                                                                                                                                                              | Payer - national health insurance                          |                                                                                                |
|                                                                                                                                                        |                                                                          | Flat fee                                                                                                                                                                                                                              | Payer - patient out of pocket and private health insurance |                                                                                                |
| Non medical costs                                                                                                                                      |                                                                          |                                                                                                                                                                                                                                       |                                                            |                                                                                                |

|                                                                                             |      |                                                  |                                   |                                                                          |
|---------------------------------------------------------------------------------------------|------|--------------------------------------------------|-----------------------------------|--------------------------------------------------------------------------|
| Work absences                                                                               | eCRF | Average daily rate for work absence              | Payer - national health insurance | Average daily allowance                                                  |
|                                                                                             |      | Daily rate to subsidise absence (private sector) | Payer - employer                  | Difference between average daily sickness benefit and average daily wage |
|                                                                                             |      | Loss of income                                   | Payer - patient                   |                                                                          |
| Complementary and alternative therapies ex. acupuncture, homeopathy, sophrology, psychology |      | Price paid                                       | Payer - patient                   |                                                                          |

\* Diagnosis-Related Groups (DRG)

The costs of healthcare are compared between the supervised and unsupervised arms for the period based on healthcare use collected prospectively at the patient level using the eCRF, hospitals' claims data. Overall quality of life will be assessed using the EQ-5D-5L, which provides a descriptive profile and a single index value for health status. The questionnaire will be filled at each follow up visit. The measure will be used for the economic evaluation, to compute QALYs.

Cumulative costs and QALYs for each trial arm will be estimated and compared in order to calculate the incremental cost utility ratio. The results will be expressed as the incremental cost per QALYs (based on the EQ-5D). We will evaluate uncertainty and estimate confidence intervals around the estimates, using both deterministic and probabilistic methods. We will account for correlation between costs and health outcomes using appropriate bivariate methods. Cost-effectiveness acceptability curves will be used to graphically represent the probability that the intervention would be cost-effective for cost-effectiveness thresholds of €50 000 and €100 000 per QALY gained (multiple thresholds for sensitivity analyses). Reporting will follow the Consolidated Health Economic Evaluation Reporting Standards statement.

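### Section 11 gives two different cost scopes, and its resource table takes emergency visits and part of hospital use from adverse-event data that no visit is scheduled to collect

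*Protocol*

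**What the plan says.** The incremental cost per QALY is a listed secondary endpoint (Protocol, section 6.2). Section 11 describes the analysis as made "from the societal perspective" over one year and states: "We will estimate costs for all healthcare use in both arms". The list that follows includes physician services, hospital stays, emergency visits, and drugs with psychotropics named explicitly.

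The resource table in the same section is narrower and names its sources:

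- Consultations and medication in ambulatory care: "Out of hospital care post discharge: only in relation with the follow up of the cognitive complaints".
- Hospitalisations and outpatient visits: "eCRF DRG* & length of stay adverse events information".
- Emergency visits to the centre that do not lead to admission: "eCRF adverse events information", with no other source in that row.

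After the table, section 11 adds hospital claims data next to the eCRF as a basis for healthcare use, without saying which items the claims cover.

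Section 10 says "there will be no collection of serious adverse events organized by the sponsor as part of the study". For suspected incidents and reactions it relies on routine care vigilance: these "must be reported by the health professional to the vigilance networks". The flow-chart (section 3) and the schedule of assessments (section 7.5) contain no adverse-event collection at T0, T1, T2 or T3. A patient diary is handed out at T0, T1 and T2. Its content is not described, and the resource table does not name it.

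**The concern.** There are two separate problems.

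The first is scope. The text and the table of one section define different cost totals, and a site filling in the eCRF can follow only one of them. If the table is followed, unrelated consultations and drugs are never recorded, and no later analysis plan can bring them back. Someone must also decide which care relates to cognition, and the trial is open-label. Experimental patients discuss their cognition with a neuropsychologist every week and controls have no such contact, so the same consultation could be classified differently in the two arms.

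The second is source. One cost line depends entirely, and another in part, on adverse-event information whose collection the protocol describes nowhere. If that information is not gathered, emergency costs may be incomplete in the cost total.

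**Working it through.** No figure in the plan is in dispute, so the main check sets the passages side by side.

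**1. Scope.** Text of section 11: every kind of healthcare use, both arms, societal perspective. Table of section 11: ambulatory consultations and drugs only where they concern the cognitive complaints. A concrete case shows that the two cannot both hold. A psychotropic prescribed by a community physician for a reason other than the cognitive complaints is in scope by the text's list and out of scope by the table. No other part of the protocol chooses between them.

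**2. Source, hospital row.** It names DRG, length of stay and adverse-event information. An admission is commonly classed as a serious event, so the adverse-event part of this row conflicts directly with section 10. The other two parts, and the claims data, remain.

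**3. Source, emergency row.** It names adverse-event information alone. Section 10 excludes serious events and is silent on non-serious ones, and an emergency visit without admission need not be serious. Section 10 therefore does not contradict this row outright. The defect is that the named source appears in no section and at no visit, while the only reporting route described leads to external vigilance networks and not to the eCRF.

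**4. Instruments already in place.** On the synopsis timing (T1 = 3 months, T2 = 6, T3 = 12), diaries handed out at T0, T1 and T2 open intervals of 3, 3 and 12 − 6 = 6 months, which together span the one-year horizon.

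**5. Scale, for illustration only.** Section 11 gives thresholds of €50 000 and €100 000 per QALY but no expected QALY gain. Assume a gain of 0.01 to 0.03. The extra cost per patient at which the ratio equals the threshold is threshold × gain:

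- €50 000 × 0.01 = €500, and €50 000 × 0.03 = €1 500
- €100 000 × 0.01 = €1 000, and €100 000 × 0.03 = €3 000

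Only a difference between arms moves the incremental cost; an equal omission in both arms cancels. If an emergency visit is assumed to cost €100 to €400, a mean difference of €300 needs 300/400 = 0.75 to 300/100 = 3 more visits per patient in one arm. On these assumptions the emergency line alone would need a large imbalance to matter. The ambulatory line covers more kinds of care, but the protocol gives nothing from which to size it.

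**The case against.** A reader might infer that the trial has declared it will collect no adverse events, so that emergency visits have no data source at all. The documents do not support that. Section 10 excludes only serious events whose collection the sponsor would organise. Section 11 names hospital claims without limiting them to admissions, and the emergency row concerns visits to the centre itself, whose own records might capture them.

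The silence of the flow-chart is also weak evidence. It has no row for prescriptions, ambulatory consultations or hospital stays either, yet the table places these in the eCRF. The undescribed diary may already be a resource-use instrument.

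Nor is bias between arms shown. The protocol does not say who judges relatedness or by what rule. Unequal attribution is a plausible consequence of open-label weekly supervision, and neither its direction nor its size is known. Finally, the analysis reports acceptability curves at more than one threshold, with deterministic and probabilistic uncertainty analysis, so there is no single pass-or-fail conclusion to overturn.

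All of this limits the source problem to an unscheduled and unclear source. It does not touch the scope contradiction, which nothing in the protocol resolves. Leaving that to an analysis plan is no answer, because the question is what gets recorded.

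**Conclusion.** The point holds in two parts. The scope contradiction is plain: following the table produces a cost per QALY other than the one the text promises, and it needs an open-label relatedness judgement that could differ by arm. The source problem is smaller. The emergency row rests only on adverse-event information that no section or visit provides for, and the hospital row rests on it in part. Claims data probably rescue admissions and may rescue some emergency visits, but the emergency row does not say so.

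The effect is confined to the secondary cost-per-QALY endpoint; the primary analysis is untouched. A reader might take the €500 to €1 500 range as evidence that the economic conclusion would reverse. It is not: it depends on an assumed QALY gain that the protocol does not give, and no cost difference between arms has been shown. The change should be made because it is cheap and the data cannot be recovered afterwards.

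**What to change.** - **Scope.** Align the table with the text: record all ambulatory consultations and medication, whatever the reason, for the base case. Keep the cognition-related subset as a sensitivity analysis, with a written rule for who classifies care and how. If the sponsor prefers the narrow scope, the text must say so and drop the claim to cover all use. That would also reconcile the section, but it keeps the relatedness judgement and fits the societal perspective less well.
- **Source.** In the emergency and hospital rows, replace the adverse-event wording with a source the trial does collect: the existing diary, a short resource-use page at T1, T2 and T3 (admissions, emergency visits, consultations, drugs), or both, cross-checked with hospital claims. State which items the claims cover. The six months from T2 to T3 are a long recall period, so the diary is worth using there.
- **Consistency.** Bring section 10, the schedule in section 7.5 with the flow-chart, and the table into agreement on what is collected, and describe what the diary records.

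The cost is one short eCRF page at visits that already take place, some diary and table wording, and a few minutes of patient recall.
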